In addition, existing research has also shown that temporary monetary incentives and targets can be used to inculcate behavioral change in domains such as gym attendance [17], smoking, work behavior [18], alcohol abuse [19], and weight loss [20]. Research studies suggest that temporary monetary incentives and specific targets can effectively reduce social media use and allow people to limit their screen time [21].

However, the current body of research does not provide evidence regarding whether self-selected targets or externally imposed targets are more effective in promoting and maintaining behavioral change, especially in the context of smartphone use, thereby improving mental health. Reducing smartphone screen time is essential for maintaining a healthy and productive lifestyle.

In this study, we aim to nudge people to reduce their screen time by providing temporary monetary incentives and targets. Target is defined as the minimum percentage reduction in daily mobile screen time from the daily average mobile screen time during the baseline period.

The objectives of the study are as follows:

To estimate the impact of monetary incentives and targets on reducing mobile screen time during the treatment and posttreatment period.To evaluate the efficacy of self-selected versus assigned targets in reducing mobile screen time.To estimate the impact of screen time reduction on mental health. Mental health will be assessed using measures such as Generalized Anxiety Disorder–7 (GAD-7) for anxiety, Patient Health Questionnaire–9 (PHQ-9) for depression, daily mood survey for mood, and well-being scores for general well-being.

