#### Intervention-1 (Self-Selected Group)

In this group, participants were asked to select a target to reduce their mobile screen time from their baseline average mobile screen time. They were presented with 3 target options (10%, 20%, and 30%) and were asked to select one of the targets. The target options were chosen such that none of the targets is unreasonably high, ensuring that there are at least some participants who chose the target. Additionally, we want to ensure that the targets are sufficiently different so that participants are not indifferent between them. During the intervention period, participants in this group were eligible to receive a monetary incentive of INR (Indian Rupee) 50 (US $0.61) per day for successfully achieving the target they selected.

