#### Intervention-2 (Assigned Group)

In this group, participants were assigned a target to reduce their mobile screen time from their baseline average. This target was determined after the participants in the self-selected group chose their respective targets. The assigned target was determined as the average of the targets selected by participants in the self-selected group. This was done such that both groups have the same average screen time reduction target, and thereby we can compare the average screen time reduction between the groups. This makes the intervention arms on average only differ in whether they chose or were assigned a screen time reduction target. During the intervention period, participants in this group were eligible to receive a monetary incentive of INR 50 (US $0.61) per day for successfully achieving the assigned target.

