#### Control Group

Control group participants were neither assigned nor asked to select a target for reducing their mobile screen. They were provided with standard information regarding the advantages of reducing their mobile screen time and received reminders to do so. They will not receive any monetary incentives for reducing their mobile screen time.

All participants, including the control group, received identical information regarding the advantages of reducing mobile screen time. All participants were informed that they would receive a fixed amount of INR 500 (US $6.06) upon completing the study. Additionally, participants in the study who report their mobile screen time every week will have the opportunity to win 1 of 2 lotteries, worth INR 5000 (US $60.55) each.

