### Statistical Analysis

We will estimate the effects of mobile screen time, target achievement rate, GAD-7, PHQ-9, and daily mood scores by comparing variables of interest between the intervention and baseline and between the postintervention and baseline periods. To perform this analysis, we will use Stata 17 and R (version 4.2.2; Free Open-Source Software). The unadjusted effects will be calculated as differences in the means and conducting a 2-tailed Student *t* test for significance. For adjusted effects, we will use simple ordinary least square regression adjusting for participant-level covariates: age, gender, and employee or student. We assume errors to be correlated within each participant but uncorrelated across participants. A separate equation will be used for each dependent variable. The regression equations are provided in Multimedia Appendix 1. For mobile screen time, we will estimate a difference-in-difference ordinary least square regression. To account for the impact of the intervention and the postintervention period, we will incorporate dummy variables for the period. Specifically, assessing the effect on mobile screen time and target achievement rate postintervention will provide valuable insights into habit formation. Multilevel or hierarchical linear modeling will also be used to allow differential relationships between mood and screen time at the individual level.

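### Own-target achievement rate has no control contrast and is scored at different thresholds in the two incentive arms, so by itself it cannot support an arm-versus-control or habit-formation conclusion

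*Protocol article*

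**What the plan says.** The Introduction defines a target as the "minimum percentage reduction in daily mobile screen time from the daily average mobile screen time during the baseline period". The three arms then stand differently towards it:

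- Self-selected group: "They were presented with 3 target options (10%, 20%, and 30%) and were asked to select one of the targets".
- Assigned group: "The assigned target was determined as the average of the targets selected by participants in the self-selected group". The reason given is "This was done such that both groups have the same average screen time reduction target", so that average screen time reduction can be compared.
- Control group: "Control group participants were neither assigned nor asked to select a target for reducing their mobile screen".

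Statistical Analysis opens with "We will estimate the effects of mobile screen time, target achievement rate, GAD-7, PHQ-9, and daily mood scores by comparing variables of interest" between each later period and baseline. It names a difference-in-difference regression for mobile screen time only. It then says that "assessing the effect on mobile screen time and target achievement rate postintervention will provide valuable insights into habit formation". The regression equations are in Multimedia Appendix 1, which is not at hand.

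**The concern.** An achievement rate is the share of days on which a person clears a set threshold. It depends on where the threshold stands as well as on what the person does. Here the threshold is absent in one arm, takes three values in another and one value in the third. The three values are chosen by the participants themselves.

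Three consequences follow:

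- With no control rate on this outcome, a within-arm change cannot be separated from calendar effects, self-monitoring, or the information and reminders that controls also receive.
- The two incentive arms can differ in achievement while their screen time is the same, or agree while it differs.
- After the incentive stops, some days fall below the target through ordinary variation. A raw postintervention rate read as persistence would count those days as habit.

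**Working it through.** The article gives no expected achievement rate or difference, so there is no stated figure to reproduce. The target values come from the intervention sections. The distributions below are assumptions and are shown as ranges.

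**1. Where the outcome is defined**

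| Arm | Target | Own-target rate |
|---|---|---|
| Self-selected | 10%, 20% or 30%, chosen after randomization | defined, three thresholds |
| Assigned | one value, mean of the chosen targets | defined, one threshold |
| Control | none | not defined |

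In the baseline period no target had yet been set in any arm. Because the target is a percentage of the baseline mean, baseline days can still be scored against it afterwards.

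**2. Days that meet a target by chance**

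Assume no behaviour change and daily screen time normal around the person's baseline mean with coefficient of variation CV. The share of days at least a fraction t below the mean is Φ(−t/CV).

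| CV | 10% target | 20% target | 30% target |
|---|---|---|---|
| 0.25 | 34.5% | 21.2% | 11.5% |
| 0.35 | 38.8% | 28.4% | 19.6% |
| 0.45 | 41.2% | 32.8% | 25.2% |

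**3. Equal mean targets do not give equal rates**

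Let daily percentage reduction be N(μ, σ) in both incentive arms, so behaviour is identical. With shares w choosing targets t, and T = Σ w·t:

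- assigned rate = 1 − Φ((T − μ)/σ)
- self-selected rate = Σ w·[1 − Φ((t − μ)/σ)]

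Example: half choose 10%, half choose 30%, so T = 20%, with σ = 10.

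- μ = 10: assigned 1 − Φ(1) = 15.9%; self-selected 0.5 × 50.0% + 0.5 × 2.3% = 26.1%; gap +10.3 points (unrounded).
- μ = 30: assigned 1 − Φ(−1) = 84.1%; self-selected 0.5 × 97.7% + 0.5 × 50.0% = 73.9%; gap −10.3 points (unrounded).
- μ = 20: both 50.0%; gap 0.

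Over five target mixes (T from 15% to 23%) and μ of 0, 10, 20 and 30%, the gap, self-selected minus assigned, runs as follows:

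| Daily SD σ (points) | Range of gap (points) |
|---|---|
| 10 | −10.3 to +10.3 |
| 20 | −2.1 to +2.9 |
| 30 | −0.7 to +1.2 |

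**4. Target-to-person fit**

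Assume each person has an achievable reduction c ~ N(m, 10) and meets the target when c is at least the target, with no daily variation. Targets are split in thirds over 10/20/30%, so T = 20%. Fall at random means choice is unrelated to c; sorted means the lowest third of c choose 10% and the highest third 30%.

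| m | Assigned | Fall at random (gap) | Sorted (gap) |
|---|---|---|---|
| 28% | 78.8% | 72.4% (−6.4) | 96.4% (+17.6) |
| 20% | 50.0% | 50.0% (0) | 50.0% (0) |
| 15% | 30.9% | 35.6% (+4.7) | 9.2% (−21.7) |

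The sign reverses between m = 28% and m = 15%. If daily reduction varies around c with SD σ, the rate is the average of 1 − Φ((t − c)/σ) over c. The sorted gaps then shrink to +5.4 (m = 28%) and −3.9 (m = 15%) at σ = 10, and to +1.2 and −0.8 at σ = 20.

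**5. What the rate does capture**

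For a fixed target and σ = 20, moving μ from 0 to 10% raises the rate by 19.1 points at a 10% target, 15.0 at 20% and 9.2 at 30%. The rate responds to behaviour, but by an amount that depends on the target.

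Scored at one common 20% threshold, a control arm with μ = 0 and an incentive arm with μ = 10% give 15.9% and 30.9% at σ = 20, and 25.2% and 36.9% at σ = 30. That contrast is defined in every arm.

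**The case against.** The strongest reply has five parts.

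- **Habit formation does not rest on this outcome alone.** The sentence names screen time too. Screen time is on a common scale, is collected in all arms through the postintervention period, and has its own difference-in-difference model. This stands. A reader might infer that the habit-formation question is left unanswered; the document does not support that.
- **The rate does reflect behaviour.** Each person's target is fixed, so a change in that person's rate between periods is a change in behaviour, and baseline days can be scored retrospectively. This stands. It would be wrong to say that the rate cannot measure behaviour change or that the baseline comparison is impossible. Retrospective scoring does not remove a time trend common to all arms, which needs a control rate.
- **No control contrast is promised.** Statistical Analysis states period contrasts, and the equations are not shown. This also stands. The point is that own-target achievement admits no control contrast, whatever the appendix says.
- **Choosing a target is the randomized intervention.** Choice after randomization is therefore not in itself a bias. Success against one's own goal is a legitimate randomized outcome for the two incentive arms, and the Discussion lists it apart from reduction. This stands for that question. It does not turn a difference in success into a difference in screen time behaviour. The Discussion itself expects the average target to lie above some people's preferred reduction and below others'.
- **The thresholds are few.** On the percentage scale there are three values in one arm and one in the other. A reader might infer that every participant has a different threshold; that is true only in minutes.

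**Conclusion.** The concern holds in a limited form. Own-target achievement has no control contrast, and equal mean targets do not make it comparable as a measure of behaviour between the incentive arms. It can serve as an outcome within those arms. By itself it cannot carry an arm-versus-control or habit-formation conclusion.

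The lack of a control contrast follows from the article's text alone. The size of the between-arm distortion does not: it rests on assumed normal models, target mixes and variances. With daily variation it may be negligible (under 3 points at SD 20 to 30 in step 3) or about 10 points either way at SD 10. The figures near 20 points need daily variation to be absent and people to sort perfectly by ability. A reader might take a large gap in a known direction from one such scenario, but the sign reverses with the assumed achievable reduction, so neither size nor direction is established.

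**What to change.** From the daily screen time already collected, compute for every participant, in all three arms and all periods, the share of reported days at least 10%, 20% and 30% below own baseline mean. Baseline days give the chance rate. Compare arms at these common thresholds. Let the comparison between arms, rather than the change from baseline alone, carry the inference, because the baseline days also form the mean they are scored against.

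Report own-target achievement only within the two incentive arms, as a secondary or descriptive measure, with baseline days scored retrospectively against the same target. Reword the habit-formation sentence so that it rests on the screen time difference-in-difference and the common-threshold rates.

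The cost is recoding of existing data and a lower standing for own-target achievement. No new data collection is needed.

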## Introduction

Smartphones have become ubiquitous in people’s lives. The global average for daily screen time is 6 hours and 37 minutes [1]. In 2021, India had a mobile subscriber count of 1.2 billion, and around 750 million of them were using smartphones [2]. The average screen time for Indians has increased to 7.3 hours [3]. As of 2019, the leading mental disorders are depression and anxiety, which affect 280 million and 301 million people worldwide, respectively [4]. Estimates suggest that over 197 million Indians, approximately 15% of our population, experience mental disorders. Of these, approximately 85 million experience depression- and anxiety-related disorders [5]. Existing research links excessive screen time to lower subjective well-being, depression, anxiety, sleep disorders, and poor physical health [6-13].

Numerous correlational studies have explored the relationship between digital media use and well-being, with many of them indicating that screen time and mobile consumption are negatively linked to subjective well-being [6-10,14]. For instance, Przybylski and Weinstein [15] explored the effect of digital media use on the well-being of adolescents, providing support for the Goldilocks hypothesis—individuals with moderate use have higher well-being than those with lower and higher use.

On the other hand, Twenge and Campbell [14] showed that although light users of digital media had higher well-being than people who abstain, moderate and heavy users had lower well-being than light users. Twenge and Martin [7] demonstrated that the associations between greater digital media use and psychological well-being are greater for female than male individuals. In their correlational study, Twenge and Campbell [14] found that individuals with moderate and heavy digital media use (smartphones, social media, and others) had lower well-being than those with lighter media use, especially individuals with greater than 5 hours of digital media use per day. Orben and Przybylski [16] used specification curve analysis to understand if there is any correlational relationship between digital media use and well-being among adolescents. They found a negative but small association, explaining at most 0.4% of the variation in well-being [16].

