#### Preregistration

Over 2 weeks, we conducted preregistration to gather expressions of interest. A total of 327 individuals expressed interest in the study. The individuals who displayed interest in the study were requested to complete the baseline survey, which included information regarding demographics, daily mobile phone time, past attempts to reduce screen time, willingness to reduce screen time, and GAD-7 and PHQ-9 for assessing anxiety and depression (a list of collected data is summarized in Table 1). Participants were also asked to report their daily mobile screen time and upload screenshots of the digital well-being app for the week before preregistration.

The digital well-being tools offer a daily overview of a person’s phone use: the number of times the user checks their phone and the screen time. The screen time measures the total and app-wise time of the phone use. Participants share their mobile screen time through a weekly survey asking them to fill in the total time in hours and minutes of screen time for each day as displayed in the digital well-being app. As proof, the participants were asked to upload a screenshot of the digital well-being app for that week. A screenshot of the digital well-being app is shown in Figure 3. The study team checks whether the screen time in the survey matched with the screenshot. The study team provided step-by-step visual instructions for the process of uploading the screenshot from the digital well-being app. Of the 327 individuals interested in the study, 207 provided consent and completed the baseline survey.

**Table 1 table1:** Data collection at various stages of the study.

Data category	Expression of interest	Baseline^a,b^	End of intervention^a,b^	End of postintervention^a,b^
Basic information and contact details	✓	✓	✓	✓
Demographic		✓		
Information on willingness, difficulty, and magnitude in reducing mobile screentime		✓		
Information about mobile use		✓		✓
Phone addiction scale	✓	✓		✓
Generalized Anxiety Disorder–7		✓	✓	✓
Patient Health Questionnaire–9		✓	✓	✓

^a^Daily mobile screen time use: participants share their daily screen time and upload screenshots of their screen time by using the digital well-being feature on their Android mobile phones through self-administered weekly surveys.

^b^Daily mood survey: mood data are collected daily through WhatsApp messages, using a 1-10 scale that is sent at varied times of the day.

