#### Intervention Period

The period of 5 weeks following the group allocation is the intervention period. During this, the participants will receive an email every Sunday asking them to report their mobile screen time for the preceding week and provide a screenshot. Two reminder emails will be sent to those who do not respond. Additionally, participants will continue to receive a daily mood survey through WhatsApp. Every Wednesday, we will send out reminders to all groups via WhatsApp with information about the benefits of reducing mobile screen time and details about 2 lotteries. Participants in both intervention groups will also receive email reminders for their chosen and assigned targets. Participants in the intervention groups will receive a daily incentive of INR 50 (US $0.61) for successfully meeting their daily target. These incentives will be transferred to the participants via the Unified Payments Interface after the intervention period. At the end of the intervention, an end-of-intervention survey will be administered to all participants.

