## Discussion

### Principal Findings

The study focuses on the impact of monetary incentives and self-selected versus assigned targets on reducing mobile screen time and thereby improving mental health and well-being during the intervention and postintervention periods.

Previous studies mainly focused on providing correlational evidence. For example, Mosquera et al [24] found that deactivating Facebook for 1 week made people less depressed and led them to engage in healthier activities. Allcott et al [25] found that deactivating Facebook for 4 weeks before the 2018 US election caused small but significant improvements in well-being, self-reported happiness, life satisfaction, depression, and anxiety. However, they did not find an effect on other well-being measures. In a follow-up paper, Allcott et al [21] monetarily incentivized people to reduce social media (Facebook, Instagram, Twitter, Snapchat, web browsers, and YouTube). The group that was monetarily incentivized over a period reduced their screen time by 56 minutes during the treatment period of 3 weeks. However, they found statistically insignificant changes in measures of happiness, life satisfaction, anxiety, and depression [21].

Compared with existing studies that have incentivized reduction over a period, this study offers everyday incentives and targets for people to reduce their overall smartphone use. While there is only 1 study that has used daily incentives, the focus of the study is on rational addiction and does not test the effects on anxiety and depression [22]. In addition, none of the studies have examined self-chosen targets versus given targets on the reduction, target achievement, and impact on well-being. Moreover. the existing studies do not study the effect of reduction on PHQ-9, GAD-7, and daily moods. Although Alcott et al [25] measured daily happiness, they did not have daily use data to understand the impact of daily use on happiness [25].

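### Objective 3 claims the effect of reducing screen time on mental health, but the trial randomizes group, and the only described analysis linking a mental-health measure to screen time is observational

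*Protocol article*

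**What the plan says.** The Introduction lists three objectives. The third is "To estimate the impact of screen time reduction on mental health", with mental health measured by GAD-7, PHQ-9, a daily mood rating and well-being scores.

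Under Randomization and Blinding, participants are allocated to control, self-selected target or assigned target in a 1:2:2 ratio. Screen time itself is not allocated.

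Statistical Analysis describes two routes to mental health.

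- **Outcome comparisons:** "We will estimate the effects of mobile screen time, target achievement rate, GAD-7, PHQ-9, and daily mood scores by comparing variables of interest", with each later period set against baseline. Differences in means are tested by t test, and least-squares models adjust for age, gender and status. Difference-in-difference estimation is named for screen time only.
- **A mood and screen-time model:** "Multilevel or hierarchical linear modeling will also be used to allow differential relationships between mood and screen time at the individual level".

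On measurement (Preregistration), participants "fill in the total time in hours and minutes of screen time for each day" in a weekly survey. Mood is collected once a day over WhatsApp, "using a 1-10 scale that is sent at varied times of the day" (Table 1, footnote b). The regression equations are in Multimedia Appendix 1, which is not shown.

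**The concern.** Screen time reduction happens after randomization and is the participant's own behaviour. Randomizing group identifies the effect of group. It does not by itself identify the effect of using the phone less.

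This matters because the article intends a causal reading. Principal Findings describes earlier work as mainly correlational and says of one earlier study that "they did not have daily use data to understand the impact of daily use on happiness". The Discussion and Conclusions repeatedly describe better mental health as following from less use, and Results looks ahead to policy guidelines on screen exposure. The Limitations section mentions neither reverse causation nor confounding. A mood and screen-time coefficient reported under Objective 3 could therefore be read as an effect of screen time when it may partly or wholly reflect the effect of mood on use, or of a third factor on both.

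**Working it through.** The article gives no figure for this point, so there is nothing to reproduce. The check sets the objective against each described analysis and then illustrates the mechanism.

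**1. What each analysis can estimate**

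| Analysis (Statistical Analysis section) | Varies by randomization? | Estimates at best |
|---|---|---|
| GAD-7, PHQ-9, mood: later period against baseline | Not if read within arm; yes if change is compared between arms | Change over time, or effect of the assigned package |
| Multilevel model of mood and screen time | No; daily use is self-chosen | Association |

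Neither row is the effect of screen time reduction. No mediation or instrumental-variable step is described, and no described model ties GAD-7 or PHQ-9 to screen time.

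**2. Why the package effect is not the screen-time effect**

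The incentive arms also have daily targets, target reminders and the prospect of cash. The maximum is 5 weeks x 7 days x INR 50 = INR 1,750. On timing, "These incentives will be transferred to the participants via the Unified Payments Interface after the intervention period". These are routes to mood that the control arm lacks, whether or not they prove important.

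**3. Timing, if mood and use are paired on the same day**

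The article does not state the pairing. If it is same-day, a rating made before the day ends precedes part of the whole-day total. Assume a waking day of 07:00 to 23:00 (16 hours) with use spread evenly. The share of use after a rating at hour h is then (23 - h)/16:

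- 09:00: 14/16 = 87.5%
- 12:00: 11/16 = 68.8%
- 18:00: 5/16 = 31.3%
- 21:00: 2/16 = 12.5%

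The share depends on prompt times that the article does not give, so only the range is informative.

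**4. Illustration with no true effect of use on mood**

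Simulated: 156 participants (the number randomized) x 77 days ((2 + 5 + 4) weeks x 7). The model is a within-person regression of mood on same-day use with participant-clustered standard errors, 200 runs. The coefficients of 0.3 and the uniform prompt times are assumptions.

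| Mechanism | Mean slope | Null rejected |
|---|---|---|
| Low mood raises later use | -0.147 | 100% |
| A daily factor moves both | -0.083 | 100% |
| Neither | 0.001 | 4.5% |

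**5. Does a previous-day model cure it?**

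Not alone. Suppose mood drives the whole day's use (coefficient 0.3) and carries over between days. The slope on previous-day use is then -0.077 at an autocorrelation of 0.3 and about -0.13 at 0.5, rejected in every run, again with no true effect. In the same set-up, adding previous-day mood brings the slope back to about zero. That happens because the set-up contains no other persistent cause, which real data cannot guarantee.

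**The case against.** The strongest reply is that Objective 3 does not rest on the mood model. GAD-7, PHQ-9 and mood are analysed first as trial outcomes, and the multilevel model is an addition whose target the article calls relationships, not effects. The equations are in an appendix, where the lag, the dependent variable and a between-arm contrast may all be specified. This stands, and it limits the point. The article cannot be faulted for details left to the appendix, nor said to lack a randomized comparison of mental health. It does not rescue the objective, because an arm comparison still answers a different question from the one Objective 3 poses.

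Four stronger readings are tempting, and the documents do not support them.

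- **Mood is regressed on same-day use.** Neither the lag nor the dependent variable is stated. Principal Findings hints at the direction but not at the lag.
- **Mood is rated before much of the use.** Prompt times are only said to vary. A late prompt follows most of the day's use.
- **The article's own literature figure shows that no mental-health effect could be detected.** The result, "explaining at most 0.4% of the variation in well-being", is a correlation in adolescents. Converting it into an expected trial effect and a power would treat a correlation as causal, which is the error at issue. Limited power is a separate matter that the Limitations section already concedes.
- **Cash demonstrably alters mood.** Payment comes after the intervention period, so during that period only anticipation could act. Reporting is weekly, and no daily pass or fail message from the study team is described.

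**Conclusion.** The point holds as a mismatch between a causal objective and the analyses described for it. The described comparisons can support, at best, a statement about the incentive-plus-target package. The mood and screen-time model can support a statement of association. Neither supports a statement about the effect of reducing screen time.

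The actual size of any bias is unknown. The simulated slopes rest on assumed coefficients and show only that ordinary mechanisms, at this number of participants and days, can produce a clearly significant coefficient when the true effect is zero. The timing concern is conditional on same-day pairing. The conclusion on the objective needs neither the simulation nor the timing argument: it follows from what is randomized. The point does not threaten the screen-time objectives. It should be corrected because it changes what the trial may conclude about mental health.

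**What to change.** 1. Restate Objective 3 as the effect of the incentive-plus-target package on mental health.
2. Answer it by comparing change from baseline in GAD-7, PHQ-9 and mean mood between the randomized arms. Say so in the Statistical Analysis section, where the between-arm difference-in-difference is now named for screen time only.
3. Report the mood and screen-time model as an association. Split use into the within-person deviation and the person's mean, add day-of-week and study-week terms, and state the pairing and how prompt time is handled.
4. If a previous-day model is used, adjust for previous-day mood as well, and still do not read it as causal.
5. Add reverse causation and confounding to the Limitations section, and align the Discussion wording with the restated objective.

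Data collection ended in November 2023 according to the abstract, so the change should be dated and marked as made afterwards. No new data are needed. The costs are a narrower stated objective and, in a previous-day model, the loss of daily pairs wherever a weekly report or a mood rating is missing. That will be more than one day for participants who skipped weeks, and the allocation week may also break the series.
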